#### Analysis of the Results

Baseline characteristics will be assessed between the active and sham treatment groups by descriptive statistics, as well as formal statistical tests. Baseline differences between the two groups, if any, will be adjusted for in the final statistical analyses. All assessment scores will be checked for normality of distribution to determine the choice of either parametric or nonparametric methods. Bartlett statistic will be used to assess the homogeneity of variances, and Levene [56] or Brown-Forsythe [57] tests, which are less sensitive to departures from normality, may also be used. In all instances, a *P* value <.05 will be considered significant.

To test H1 and H2 (the efficacy of rTMS treatment), two-factor (active vs sham) repeated (pre-post treatment) analysis of variance (ANOVA) will be used to investigate the effect of treatment before and after the 4-week block of treatment. The dependent variable will be the change in the ADAS-Cog score (primary outcome measure). Testing H3 will be similar to the tests of H1 and H2, but the two factors will be the two durations of treatment.

For secondary outcome measures, a two-factor ANOVA will also be used in the same way as described above, but a Hochberg test [58] will be applied to correct for multiple comparisons.

The last-observation-carried-forward method will be used in the case of missing data or premature termination.

To test H4 (the durability of rTMS treatment), repeated measure ANOVA will be used among responders (those who show improvement in the ADAS-Cog score of ≥3 points over the course of treatment [3] in both groups) to investigate the duration over which the improvement may last. Post-hoc follow-up methods, such as Dunnett [59] and Tukey [60] tests, will be applied as needed. In addition, a mixed regression model will be developed to predict the response variable at each assessment visit of the active treatment group (both treatment arms separately). The independent variables will be patients’ current age and the severity of Alzheimer disease (as measured by the CDR).

To test H5 (the correlation of treatment effect and severity), we will run regression and correlation analyses between the severity of Alzheimer disease (the MoCA and CDR scores) at baseline and the change in the ADAS-Cog score. The correlation coefficient (either the Pearson or Spearman correlation coefficient, whichever is more appropriate) and its statistical significance will be determined. Sensitivity of the regression and correlation analyses with respect to the data distribution will be assessed. Influential observations and outliers, if any, will be identified.

The above statistical analysis will also be repeated for secondary outcome measures after correcting for multiple comparisons. In addition, covariate analysis will be performed in an appropriate manner. Covariance balance (or imbalance) is checked with the ANOVA test when there are three or more groups or by the *t* (or the approximate Z) test when there are only two groups. For the ANOVA test, we will first check the satisfaction of ANOVA assumptions (such as normality of distribution and equality of variances). If any violation is found, transformations will be made before the ANOVA test. If covariance imbalance is statistically significant, the final data analysis will be adjusted for covariance imbalance (eg, by the use of regression analysis with these imbalanced covariates as explanatory variables).

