### Study Goal, Objectives, and Hypotheses

The overall goal of this study is to compare the efficacy of high-frequency active versus placebo rTMS for the treatment of cognitive impairment among people with mild to moderate Alzheimer dementia. The specific objectives and hypotheses of the study are as presented below.

First, estimate the difference in treatment effects among patients treated with active as compared with placebo high-frequency rTMS applied bilaterally to the DLPFC. Hypothesis 1 (H1) is as follows: better cognitive performance will be seen in patients randomly assigned to the active treatment group compared with those assigned to the placebo group.

Second, estimate the difference in treatment effects for patients receiving 4 weeks of rTMS versus 2 weeks of rTMS. Hypothesis 2 (H2) is as follows: four weeks of rTMS will be more effective than 2 weeks of rTMS in improving cognitive function.

Third, estimate the duration of treatment effects among responders to active rTMS, where response is defined as improvement in the ADAS-Cog of ≥3 points. Hypothesis 3 (H3) is as follows: treatment effects will still be detectable 8 weeks postintervention, although not necessarily at 16 and 24 weeks postintervention.

Fourth, estimate the effect of dementia severity on treatment outcomes among patients receiving active rTMS. Hypothesis 4 (H4) is as follows: the effect size will be greater in participants with a clinical dementia rating (CDR) of 1 than in those with a CDR of 2.

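### The primary ADAS-Cog model is left to baseline and normality checks instead of being fixed with baseline score, age stratum and CDR stratum, and H2 sits under the wrong label

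*Protocol article*

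**What the plan says.** All of this is in the protocol article, mostly in Analysis of the Results.

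- **Primary test.** For H1 and H2, a "two-factor (active vs sham) repeated (pre-post treatment) analysis of variance (ANOVA) will be used to investigate the effect of treatment". The next sentence reads "The dependent variable will be the change in the ADAS-Cog score (primary outcome measure".
- **Baseline testing.** "Baseline characteristics will be assessed between the active and sham treatment groups by descriptive statistics, as well as formal statistical tests".
- **First adjustment rule.** "Baseline differences between the two groups, if any, will be adjusted for in the final statistical analyses".
- **Second adjustment rule.** "If covariance imbalance is statistically significant, the final data analysis will be adjusted for covariance imbalance".
- **Other covariate wording.** "covariate analysis will be performed in an appropriate manner".
- **Choice of method.** "All assessment scores will be checked for normality of distribution to determine the choice of either parametric or nonparametric methods".
- **Hypotheses.** Study Goal, Objectives, and Hypotheses defines four. H2 there is that "four weeks of rTMS will be more effective than 2 weeks of rTMS in improving cognitive function"; H3 is durability and H4 is severity. Analysis of the Results puts the two durations under H3, durability under H4 and severity under an H5 that is not defined.
- **Design.** Randomization stratifies by age (under 70, or 70 and over) and CDR (1 or 2). In the analysis section, the only group model that names age and CDR together is a prediction model within the active arms.

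**The concern.** The two adjustment rules have different triggers. Some difference in baseline means is always present, so the first rule read literally adjusts every time; the second adjusts only after a significant test. In randomised groups such a test asks whether chance produced the imbalance, which is known already. It says nothing about whether the covariate predicts outcome, and that is what makes adjustment worthwhile. The normality check adds a second fork. Two analysts following this text could report different primary P values from the same data.

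The test description adds to the uncertainty. A change score has one value per participant per visit, so a pre-post factor has no levels to cross with it. The only between-group factor named for H1 and H2 is active versus sham, which cannot answer H2 as the objectives define it.

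The prespecification of the primary result is at stake, and so is precision that data already collected could supply.

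**Working it through.** **Inputs from Sample Size Estimation:** difference 3 points, SD 4.9 (not stated whether of raw score or of change), power 80%, alpha 0.05 with Bonferroni for three groups, 63 per group. **Assumed:** pre-post correlation ρ from 0.5 to 0.9, equal pre and post variances and, for the power figures only, that 4.9 is the SD of change.

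**1. The plan's own figure.** n = 2[SD(z_α + z_β)/d]².
- z = 2.58 and 0.84 (two-sided 0.01): 2 × (4.9 × 3.42/3)² = 62.4, rounded up to 63.
- Two-sided 0.05/3, the correction as stated: 56.

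The stated 63 thus matches alpha 0.01. That is a separate matter; 63 per arm is used below only as the planned size.

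**2. Variance.** With raw SD σ:
- variance of change = 2σ²(1 − ρ)
- ANCOVA residual variance = σ²(1 − ρ²)
- ratio = (1 + ρ)/2

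The ratio does not depend on which SD the 4.9 is.

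**3. Power and error.** The adjust-if-significant rule was simulated with 20,000 replicates, two arms of 63, baseline ADAS-Cog as the only covariate and a trigger at 0.05. Power is at two-sided 0.05/3, type I error at nominal 0.05.

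| | ρ = 0.5 | ρ = 0.7 | ρ = 0.9 |
|---|---|---|---|
| Variance ratio, ANCOVA to change | 0.75 | 0.85 | 0.95 |
| ANCOVA residual SD (change SD 4.9) | 4.24 | 4.52 | 4.78 |
| Power, conditional rule | 85.1% | 84.7% | 84.5% |
| Power, always ANCOVA | 93.5% | 89.8% | 86.1% |
| Overall type I error, conditional rule | 4.3% | 4.6% | 4.8% |
| Type I error if baseline P is 0.05 to 0.20 (left unadjusted) | 8.4% | 6.7% | 5.7% |

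The power differences are 8.4, 5.1 and 1.6 percentage points. The last row rests on about 15% of replicates (roughly 3,000), so its standard error is about √(0.06 × 0.94/3000) = 0.4 points, and the 5.7% is within two standard errors of 5%. The normality step was not simulated.

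**4. How often the model would change by chance.** With k independent baseline tests at 0.05, the chance of at least one trigger is 1 − 0.95^k: 14% for k = 3 and 23% for k = 5.

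**5. Which term is tested.** On raw scores with two time points, the group-by-time interaction is the same test as a two-group comparison of change. The group main effect is not. It averages pre and post, so the effect is 1.5 points with SD σ√((1 + ρ)/2), and power at 63 per arm and 0.05/3 would be 34%, 17% and 5% for ρ of 0.5, 0.7 and 0.9. The text does not name the term.

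**6. Arms and visits.** Experimental Design lists three assignments (2-week, 4-week, sham). Randomization describes sham or active as well as 2 or 4 weeks, with block size 3. Interim Analysis and Plausible Changes to the Protocol labels four arms, G1 to G4. Outcome Measures shifts only the last three visits by duration, so weeks 3 and 5 appear common to all arms. If so, at week 5 the 2-week arm has been off treatment about 4 − 2 = 2 weeks longer than the 4-week arm.

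**The case against.** Much of this can be read charitably, and several stronger readings fail.

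- **That the primary test is invalid.** A reader might infer this from the pre-post factor on a change score. The outcome is defined as change in the Abstract and in Outcome Measures, and the interaction on raw scores tests exactly that. The intended test can be recovered, and nothing in the text points to the group main effect. This part is mostly wording.
- **That H2 goes untested.** It does not: the two durations are compared under the label H3. The shift in numbering is largely editorial.
- **That the reference to a 4-week block excludes the 2-week arm.** Baseline versus week 5 fits every arm if weeks 3 and 5 are common visits.
- **That choosing the model after looking raises the false-positive rate.** The simulation does not show this for the baseline-trigger rule, which is slightly conservative overall.
- **That adjustment happens only after a significant test.** One sentence says so. Another adjusts for any difference, and a third promises covariate analysis without detail.
- **That a fixed number of participants is lost.** No correlation is given, and if 4.9 is the SD of change, an unadjusted test with 63 per arm already has about 85% power at 0.05/3. The planned 80% is not lost.
- **That site must be in the model.** Site is not a stratification factor.

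A condensed article may also leave the full covariate list to an analysis plan. That does not answer the point, because the article states a data-dependent rule rather than staying silent.

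**Conclusion.** The point holds in a limited form and should be acted on. As written, baseline tests and a normality check choose the primary model, the two adjustment rules disagree, and neither the stratification factors nor baseline ADAS-Cog are fixed in the H1/H2 test. That test names only active versus sham, so the label H2 does not match the objective.

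The harm is a primary model not fixed in advance, lost precision, and conditional error above nominal when moderate imbalance is left unadjusted, clearest at low ρ. The size depends on the assumed ρ: it is modest at 0.9 and material at 0.5. It covers baseline ADAS-Cog only. The effect of the normality step on error is unknown.

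**What to change.** State one primary model before any comparison by arm is run, including the planned interim analysis:

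- Outcome: ADAS-Cog change (or post score) at one named post-treatment visit.
- Terms always included: randomised group, baseline ADAS-Cog, age stratum and CDR stratum. Site is optional.
- H1 (active versus sham) and H2 (4 versus 2 weeks) as named contrasts of that model.
- No baseline significance tests and no conditional adjustment; describe baseline by arm only.
- Rank-based or transformed analyses as sensitivity analyses.
- Hypothesis labels aligned with Study Goal, Objectives, and Hypotheses.

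Two things come first. Reconcile Experimental Design, Randomization and the interim analysis section on whether sham has one or two durations, because this decides how the group factor is coded. If week 5 is the named visit, state that its 4 versus 2 week contrast compares arms at different times since last treatment.

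The cost is wording. Age and CDR are recorded for randomisation and ADAS-Cog is measured at baseline, so no new data are needed.

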### Outcome Measures

Each participant will attend six assessment days in total as follows: baseline (week 0) and week 3, week 5, week 8, week 16, and week 24 posttreatment sessions. At each assessment day, three assessments will be given to the participant in the following fixed sequence: ADAS-Cog, verbal fluency test, and Stroop test. Only the patient and the research personnel designated to administer assessments will be in the room during assessments. At the baseline and week 5 and week 16 posttreatment assessments, additional caregiver assessments will be performed. Alzheimer Disease Co-operative Study-Activities of Daily Living Inventory (ADCS-ADL) and Neuropsychiatric Inventory Questionnaire (NPI-Q) assessments will be performed at each of these visits (in that order), while the Treatment Satisfaction Questionnaire for Medication (TSQM) will only be used at the week 5 assessment. These outcome measures must be administered to the same caregiver at each visit. If a participant is accompanied to an assessment visit by someone other than their usual caregiver, the assessor will contact the usual caregiver by phone to complete these assessments.

All assessments will be performed on a Monday or the first working day of the week. Note that the specific dates of the last three assessments (the follow-up assessments) will be adjusted based on whether the participant is in a 2-week or 4-week treatment group. An assessor will be assigned to each participant. That same assessor must perform all of the six assessments with the assigned participant. Deviations should be justified (changes in staff, assessor illness, etc), and an explanation will be documented in the assessment notes.

As participant schedules are often busy, we can adjust the specific dates of the assessments within ranges (Table 1). If no assessment is possible within these windows, the assessment will be skipped and the data point will be missing from the analysis (with the exception of the baseline assessment, which will require rescheduling the treatment).

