### Statistical Analysis

#### Sample Size Estimation

The sample size for the hypothesis that one group’s mean is statistically significantly different from the other (assuming two equally sized groups, which is the case in this study) can be calculated using the following formula [55]:

where *Z_α_* is the upper tail critical value in the standard normal distribution at the α level of significance (it is 1.96 and 2.58 for 5% and 1% significance levels, respectively), *Z_β-1_* is the normal deviate at 1−β% power with β% of type II error (it is 0.84 and 1.28 for 80% and 90% power, respectively), and *σ* and *d* are the standard deviation and difference of means of the two groups, respectively. The calculated N is the number of subjects in each group.

Using the above formula with a significance level of .05 (corrected using the Bonferroni adjustment for three treatment groups), an expected difference of 3 points on the ADAS-Cog score (derived from a study by Rabey et al [7], which also used ADAS-Cog as a primary outcome measure), a standard deviation of 4.9 points (derived from the results of our own pilot study [8]), and a power level of 80%, the minimum sample size is estimated to be 63 participants per group (189 in total). Allowing for 10% drop out, we will need to enroll at least 208 patients in the study to achieve this power.

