## Results

### Recruitment and Enrollment

As of November 1, 2020, we have screened 523 individuals, out of which 133 were eligible and have been enrolled. Out of the 133 individuals enrolled and randomized to the intervention groups, 104 have completed the study and 20 have discontinued the study or have withdrawn for various reasons at various stages of the study. Data of some withdrawn individuals who completed the study up to week 8 or 16 are still usable for analysis. Three individuals withdrew because they found the treatment uncomfortable, nine withdrew with no reason given, and eight were withdrawn by the site PI. Out of the eight withdrawn by the site PI, two were withdrawn for safety reasons as they developed some illnesses, although they were not related to the rTMS treatment, four were noncompliant (changed their medication during the study) or found the rTMS pulses unbearable, and two could not finish the treatment due to pandemic lockdown.

Recruitment and enrollment have been slower than initially anticipated, and the pandemic has slowed these even further. Before the pandemic, the realistic recruitment rate was one per month.

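### Last observation carried forward, the only stated missing-data rule, tends to overstate persistence at weeks 8 to 24 and conflicts with the visit-window rule

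*Protocol article*

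**What the plan says.** Protocol article, Analysis of the Results: "The last-observation-carried-forward method will be used in the case of missing data or premature termination". No exception and no sensitivity analysis is given.

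Protocol article, Outcome Measures, on visits that cannot be held within the ranges of Table 1: "If no assessment is possible within these windows, the assessment will be skipped and the data point will be missing from the analysis". Only baseline is exempt, because treatment is then rescheduled.

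Protocol article, Recruitment and Enrollment, reports that of 133 enrolled by 1 November 2020, "104 have completed the study and 20 have discontinued the study or have withdrawn for various reasons". It adds: "Data of some withdrawn individuals who completed the study up to week 8 or 16 are still usable for analysis".

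Three other statements bear on the rule:
- The Background section says that current treatment only slows progression, and that the benefit of stimulation wears off over 2 to 3 months.
- The hypothesis on duration (H3 in Study Goal, Objectives, and Hypotheses; labelled H4 in Analysis of the Results) expects an effect at 8 weeks but not necessarily at 16 or 24.
- That hypothesis is tested by repeated-measures ANOVA among responders, defined by an ADAS-Cog improvement of at least 3 points.

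**The concern.** Carrying the last score forward assumes that a participant who leaves neither declines nor loses benefit afterwards. The article's own premises contradict both parts of that assumption, and how long benefit lasts is one of the questions the trial asks. The rule therefore supplies part of the answer.

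The responder analysis is the clearest case. A responder last seen at the end-of-treatment visit is entered as improved by at least 3 points at weeks 8, 16 and 24, by construction. The ANOVA then treats those filled-in values as observed.

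There is also a practical conflict. For the same out-of-window visit, one section leaves the value out and the other fills it in. An analyst cannot follow both literally.

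**Working it through.** **Inputs.** From Recruitment and Enrollment: 133 enrolled, 104 completed, 20 discontinued. From Sample Size Estimation: a 3-point difference, SD 4.9, 63 per group, 189 in total, 10% dropout, 208 to enrol. Score trajectories after week 5 are assumptions, because the article gives none.

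**The plan's own figures.**
- Per group: 2 × (4.9 × (2.58 + 0.84) / 3)² = 62.4, rounded up to 63. This uses the 1% critical value.
- Enrolment: 189 × 1.10 = 207.9, rounded up to 208.

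**Loss so far.** 20/133 = 15.0% of those enrolled. Of those with a known outcome, 20/(104 + 20) = 20/124 = 16.1%. The other 133 − 104 − 20 = 9 are still in the study. The plan allowed 10%.

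**Week 24, equal loss.** Score improvement as positive. Assume the active arm gains 3 points at week 5 and sham 0, both arms stand at −D by week 24 (no true difference), and a proportion p of each arm leaves just after week 5.
- Active with carry-forward: (1 − p)(−D) + 3p
- Sham with carry-forward: (1 − p)(−D) + 0
- False difference: 3p

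| p | False week-24 difference |
|---|---|
| 10% | 0.30 |
| 15.0% | 0.45 |
| 16.1% | 0.48 |

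The frozen decline cancels between arms, but the frozen gain does not. Against the 3-point design effect, 0.45 to 0.48 is 15 to 16%. The standard error of a two-arm contrast at 63 per group is 4.9 × √(2/63) = 0.87, so the false difference is roughly half a standard error.

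**Week 24, unequal loss.** With loss pA in active and pS in sham, the false difference is 3pA + D(pA − pS). Take D = 2:
- pA = 25%, pS = 5%: 0.75 + 0.40 = +1.15
- pA = 5%, pS = 25%: 0.15 − 0.40 = −0.25

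The sign is therefore not fixed.

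**Active responders.** Starting from a 3-point gain and truly at −D by week 24, the upward bias is p(3 + D). For D from 0 to 3 this is 0.30 to 0.60 at 10%, 0.45 to 0.90 at 15.0%, and 0.48 to 0.97 at 16.1%.

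**Week 5.** Table 1 places this visit after the final treatment, so I take it as the primary post-treatment assessment. A participant lost before any post-baseline score is given a change of 0. If a proportion p is lost this way in both arms, a true difference of 3 becomes 3(1 − p): 2.70 at 10% and 2.55 at 15.0%. With 63 per group, two-sided alpha 0.01 and SD held at 4.9, power falls from 80.5% to 69.7% and 63.4%. Carrying a week-3 score forward could move the result either way.

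**The case against.** The strongest reply is that the size and direction are largely unknown, and much of this stands.
- Some leavers reached week 8 or 16, so less fading is frozen for them. Two could not finish treatment because of lockdown, and others may also have left before week 5. Treating all 20 as last seen at week 5 therefore gives an upper-end figure.
- The hypothesis claims detectability only at 8 weeks, whereas the illustration is for week 24. At week 8 the bias is smaller to the extent that less has faded and fewer have left.
- Loss by arm is not reported, and the Treatment Protocol section describes a sham coil that sounds and feels like the active one. Withdrawals tied to the pulses ("Three individuals withdrew because they found the treatment uncomfortable", plus an unstated share of four others) make unequal loss plausible but do not show it. Those people would tend to leave during treatment and so carry baseline or week 3 forward, not a peak score.

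A reader might also infer that the article contains three competing rules, the third admitting data only from those who reached week 8 or 16. The text does not support this. That sentence is a status report about some withdrawn participants; it does not exclude earlier leavers or rule out carrying their values forward.

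The window rule could be read together with carry-forward: the visit yields no value, and the missing-data rule then fills it. But a value described as "the assessment will be skipped and the data point will be missing from the analysis" would then be in the analysis after all, so the wording still needs to be reconciled.

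Finally, the statistical analysis plan may hold more detail. The carry-forward rule, however, is an explicit choice in the article, not a detail left open.

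**Conclusion.** The point holds for durability. As the only stated rule, carry-forward contradicts the article's own account of the disease and of the effect, and it tends to overstate persistence at weeks 8 to 24, above all among responders. The false between-arm difference at week 24 is about 0.45 to 0.48 points if the week-5 gain is 3 points, the true week-24 difference is zero, and 15 to 16% of each arm leaves after week 5. The bias among active responders could approach 1 point if they also fall 3 points below baseline.

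A reader might infer that every post-treatment visit is biased toward persistence, or that the active-sham contrast is necessarily flattered. Neither follows. At week 5 baseline carry-forward attenuates the effect, and with heavier sham loss the week-24 contrast can turn against active treatment. Nor can a definite understatement of the standard error be derived, since that depends on the spread of the carried values and on the model used for comparison.

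A rule whose bias changes direction by visit, and depends on unreported dropout timing, is unsuitable as the main rule. The conflict with the visit-window wording is a separate, smaller defect.

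**What to change.** - Replace carry-forward as the main rule with a likelihood-based mixed model for repeated measures, with arm by visit and baseline, fitted to all observed ADAS-Cog visits of every randomised participant. Include the week-3 and week-5 scores of those who later left.
- Use the same observed-data approach for the durability analysis among responders.
- Add one missing-not-at-random sensitivity analysis, for example one in which active-arm dropouts follow the sham trajectory after leaving. Keep carry-forward at most as a supplementary analysis.
- Reword the visit-window paragraph in Outcome Measures so that one missing-data rule applies throughout, and state in the status report that data from all withdrawn participants are handled under it.
- Tabulate loss by arm and by last visit attended, so that the direction of any remaining bias can be judged.

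The cost is analysis-plan wording and modest programming. The plan already includes a mixed regression model for the active arms, no new data are needed, and the change should be made before unblinding.

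### Durability is tested among responders selected on the outcome, with no stated active-versus-sham contrast, so improvement from baseline at week 8 cannot be told apart from regression to the mean

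*Protocol article*

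**What the plan says.** Under Study Goal, Objectives, and Hypotheses, the third objective is to "estimate the duration of treatment effects among responders to active rTMS, where response is defined as improvement in the ADAS-Cog of ≥3 points". Its hypothesis, H3, is that "treatment effects will still be detectable 8 weeks postintervention, although not necessarily at 16 and 24 weeks postintervention".

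Under Analysis of the Results the same question carries another label: "To test H4 (the durability of rTMS treatment". The method is that "repeated measure ANOVA will be used among responders (those who show improvement in the ADAS-Cog score of ≥3 points over the course of treatment", and the sentence continues "in both groups) to investigate the duration over which the improvement may last". Then: "Post-hoc follow-up methods, such as Dunnett [59] and Tukey [60] tests, will be applied as needed". A further analysis is added: "a mixed regression model will be developed to predict the response variable at each assessment visit of the active treatment group", with age and CDR as predictors and the two active arms modelled separately. For missing visits, "The last-observation-carried-forward method will be used in the case of missing data or premature termination".

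The active-versus-sham test for efficacy in that section is a pre-post comparison around the treatment block. No between-arm comparison is stated for weeks 8, 16 or 24. Yet the Abstract (Methods and Conclusions) presents the trial as addressing both short- and long-term effects against sham.

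**The concern.** A participant becomes a responder by having a post-treatment ADAS-Cog score at least 3 points better than baseline. Part of any such gain is chance: a baseline score that happened to be poor, or a post-treatment score that happened to be good. If later visits are compared with the same baseline, the chance-poor baseline is still in the difference, so some improvement remains even when nothing has persisted. If they are compared with the post-treatment visit, the chance-good score drops out and the group appears to worsen.

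A randomised control arm would cancel both effects, but the plan does not state that contrast for the follow-up visits. What is at stake is the third objective. The Abstract already anticipates an effect lasting up to 3 months, and the planned analysis cannot show whether such a finding reflects treatment.

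**Working it through.** The article gives no figure for the durability analysis, so there is none to reproduce. The inputs come from Sample Size Estimation: SD 4.9, expected difference 3 points, 63 per group in three groups (126 active, 63 sham). The 63 itself follows from the listed z values: 2 × (4.9 × (2.58 + 0.84) / 3)² = 62.4. A two-sided 0.05/3 gives 56 instead, but this does not affect the point here.

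**Assumptions not in the article:** 4.9 is the SD of *change* (the article does not say which SD it is); change is normal; there is no treatment effect at any visit. In the base case there is also no natural decline, and the correlation between visits is equal. Equal correlation between visits makes two changes sharing a baseline correlate at 0.5.

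**Step 1, selection.** P(change ≥ 3) = 1 − Φ(3/4.9) = 1 − Φ(0.612) = 0.270, or about 34 of 126 active participants. Their mean apparent gain is 4.9 × φ(0.612) / 0.270 = 6.0 points.

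**Step 2, what remains at week 8 against baseline.** Expected gain = correlation × 6.0, which is 1.8, 3.0 and 4.2 points for correlations of 0.3, 0.5 and 0.7. If visit correlations decay with time (0.8 baseline to post, 0.7 baseline to week 8, 0.8 post to week 8), the slope is (1 − 0.7 − 0.8 + 0.8) / (2 × (1 − 0.8)) = 0.75, leaving 4.5 points.

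**Step 3, how often this tests as significant.** In 4,000 simulated trials with no effect, using t tests at 0.05 in place of the visit contrasts:

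| Setting | Points left at week 8 vs baseline | Significant |
|---|---|---|
| Base case, 126 active | 3.0 | 96% |
| One active arm of 63 | 3.0 | 74% |
| SD of change 3 to 6 | 2.3 to 3.4 | 94% to 96% |
| Natural decline 0.5 by week 8 | 2.5 | 89% |
| Natural decline 1 | 2.0 | 71% |
| Natural decline 1.5 | 1.5 | 48% |
| Natural decline 2 | 1.0 | 26% |

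The decline values are assumptions.

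**Step 4, the other reference visit.** In the same base-case data, responders worsen by 6.0 − 3.0 = 3.0 points from post-treatment to week 8, significant in 96% of trials.

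**Step 5, active against sham responders.** With no effect, the difference is 0.0 points and is significant in 4.9% of trials. Now let there be a real 3-point effect post-treatment. Half of the active participants pass the cut, and their mean chance excess is 4.9 × φ(0) / 0.5 = 3.9 points. If nothing persists, active responders keep 0.5 × 3.9 = 1.95 points at week 8 and sham responders keep 3.0, a difference of about −1.0 where the truth is 0. If the full 3 points persist, the difference is 3 + 1.95 − 3.0 = 1.95 where the truth is 3. The simulation gave −1.04 and 1.94.

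**Step 6, all randomised participants, active against sham at week 8.** Type I error is 4.9%. Power for a persisting 3-point effect with 126 versus 63 is 97.6% by simulation. In closed form, 3 / (4.9 × √(1/126 + 1/63)) = 3.97, and Φ(3.97 − 1.96) = 97.8%.

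**The case against.** The strongest reply rests on the words *in both groups*. The section opens by speaking of the active and sham groups, so sham responders may well be included. Regression to the mean would then cancel when there is no effect (Step 5). This reading is fair, but it does not rescue the plan. Objective 3 speaks only of responders to active treatment, so the phrase could equally mean the two active durations. No between-group contrast is stated. A comparison of responders also conditions on a post-randomisation outcome, which biases it whenever there is a real short-term effect.

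Other parts of the defence stand and limit the point:

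- The plan names no reference visit. Apparent persistence arises only against baseline; against the post-treatment visit the artefact works against H3.
- The responder ANOVA is not the only follow-up analysis. The mixed regression in the active group is not stated to be limited to responders. It has no sham term, however, so it does not test durability against control.
- Natural decline shrinks the artefact, and pooling the two active arms is itself an assumption.

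A reader might infer that an inert treatment would be reported as working at week 8 and then fading just as H3 predicts. The documents do not support that. Under the equal-correlation model, the expected gain is 6.0 points post-treatment and then 3.0 at weeks 8, 16 and 24 alike, so there is no fading after week 8. The pre-post active-versus-sham test is also not restricted to responders, would usually be negative for an inert treatment, and would colour how the durability result is read.

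**Conclusion.** The point holds in this form: durability is assessed in participants selected on the outcome, with neither a reference visit nor an active-versus-sham contrast stated at weeks 8, 16 or 24, so improvement from baseline among them is confounded with regression to the mean. In the base case the artefact at week 8 equals the 3-point difference the trial is sized on. It is smaller under natural decline, but false significance against baseline still runs at 26% with an assumed 2-point decline. LOCF adds to it by carrying the selected gain into later visits.

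The size rests on reading 4.9 as the SD of change and on assumed correlations; the direction, given the reference visit, does not depend on the exact values. It concerns a stated objective but not the primary pre-post comparison.

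**What to change.** Make the inferential durability test the active-minus-sham difference in ADAS-Cog change from baseline at weeks 8, 16 and 24 in all randomised participants, estimated from one longitudinal mixed model. Fit it to observed visits rather than to carried-forward values. State whether the active arms are pooled. If each is compared with sham separately (63 versus 63), closed-form power for a persisting 3-point effect at two-sided 0.05 is Φ(3 / (4.9 × √(2/63)) − 1.96) = Φ(1.48), about 93%. Testing week 8, then 16, then 24 in fixed order is an option, not a requirement.

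Keep the responder curves as descriptive, with sham responders shown beside active ones. Reword objective 3 to match, and align the hypothesis labels: durability is H3 in the objectives and H4 in the analysis section.

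The cost is that the responder analysis loses its inferential status and the wording of objective 3 changes, so this goes beyond an edit to the analysis text. No added visits or participants are needed.
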